### Training the therapists to deliver the interventions

Four rehabilitation teams deliver the multidisciplinary rehabilitation treatment.
Each team consists of one or two rehabilitation physicians or physician
assistants (under supervision of a rehabilitation physician), one or two
psychologists/behavioural therapists, two social workers, two physical
therapists and two occupational therapists. Six other psychologists/cognitive
behavioural therapists deliver the cognitive behavioural therapy in the four
participating rehabilitation centres. The psychologists of the CBT group are not
involved in the multidisciplinary rehabilitation treatment and meetings with a
supervisor will be organised separately for both groups of psychologists.

#### CBT

All psychologists and behavioural therapists are trained in CBT. A 3-day
workshop before the start of the study was held, guided by an external CBT
expert, who is acquainted with the CBT protocol [38,43] to ensure that
execution of CBT is similar and up to standard in each centre. During the
trial seven supervision meetings are organised in which audiotaped sessions
provided during the trial are used to evaluate the therapy. Therapists are
free to contact their supervisor when questions arise.

#### MRT

Before the beginning of the study, the therapists of RRCB, who work with the
protocol for at least 5 years, organised separate workshops for each
involved discipline and a multidisciplinary team meeting in which the
therapists got acquainted with the MRT protocol. During the trial two
disciplinary supervision meetings and two multidisciplinary team supervision
meetings will be held. Therapists are free to contact their supervisor when
questions arise.

### Recruitment of patients

The inclusion of new patients took place from November 2008 until January 2011.
Potential referrers of patients to the four rehabilitation centres were informed
about the developments of the trial by newsletters four times during the trial.
Several articles on Internet sites and in magazines of patient support groups
were published to inform patients about the trial and how they could be
referred.

### Outcome measures

#### Primary outcome measures

Primary outcome parameter:

 Fatigue severity is assessed by a subscale of the Checklist Individual
Strength (CIS) [44,45]. The subscale consists of eight items, each scored
on a 7-point Likert scale (range 8–56). Validity and reliability of
the scale are good [44,46].

 Quality of life is assessed by the Short-Form 36 (SF-36) [47]. The SF-36 has eight subscales:
physical functioning (10 items), role-physical (4 items), bodily pain (2
items), general health (5 items), vitality (4 items), social functioning (2
items), role-emotional (3 items) and mental health (5 items). Every subscale
is transformed into ratings on a scale of 0 (limited in all activities) to
100 (able to carry out vigorous activities). The validity and reliability of
every subscale are high [48].

#### Secondary outcome measures

Secondary outcome parameters are:

 1. Psychological symptoms will be measured with the Symptom Check List-90
(SCL-90). The SCL-90 is a multidimensional questionnaire designed to screen
for a broad range of psychological problems. The questionnaire consists of
90 items. Each item is scored on a 5-point Likert scale (0 is ‘not at
all’ and 4 is ‘extremely’) [45,49]. The items are
combined in the following primary symptom dimensions: somatisation,
obsessive-compulsive, interpersonal sensitivity, depression, anxiety,
anger-hostility, phobic anxiety, paranoid ideation and psychoneuroticism
(total score of the SCL-90). The validity and discriminating validity are
good [50].

 2. Self-efficacy will be measured with the Self-Efficacy Scale-28 (SES 28)
to compare sense of control in relation to CFS complaints [25,45]. The scale
consists of seven questions. Items are scored on a 4-point Likert scale. The
total score ranges from 7 to 28. A higher score means more sense of
control.

 3. Causal attributions will be measured with the Causal Attribution List
(CAL) [25]. The CAL assesses whether
the patient is likely to attribute complaints to physical or non-physical
causes. The list consists of ten questions scored on a 4-point Likert scale.
Total subscale scores of physical and non-physical attributions range from 5
to 20. A higher score indicates a stronger conviction.

 4. Present-centred attention-awareness, which is foundational to
mindfulness, will be measured with the Mindfulness Attention Awareness Scale
(MAAS) [51]. The validity and
reliability of the Dutch version of the MAAS are good [52]. The MAAS consists of 15 statements
scored on a 6-point Likert scale. The mean total score ranges from 1 to 6. A
higher score indicates a greater awareness of present experiences.

 5. A patient’s personal treatment goals will be measured with the
Patient-Specific Complaints and Goals questionnaire (PSCG) [53]. The patient selects three activities
that he/she perceives as important in his/her daily life and wants to
improve. The patient rates the performance of the activity on a 100-mm
visual analogue scale (VAS). The left side of the VAS is marked as ‘no
problems at all’. On the right side the VAS is marked
‘impossible’. The PSCG is a valid and reliable measure with
sufficient responsiveness [53].

 6. Sickness Impact Profile-8 will be used to measure the impact of disease
on both physical and emotional functioning [54]. The SIP-8 is derived from the SIP. The SIP8
has eight subscales: home management, mobility, alertness behaviour,
sleep/rest, ambulation, social interaction, work, and recreation and
pastimes. Psychometric research has indicated that the SIP is reliable and
valid [55,56].

 7. Physical activity will be measured by a multisensor armband (Sense Wear
Pro Armband; BodyMedia, Inc., Pittsburgh, PA). The armband was developed to
measure energy expenditure by integrating accelerometry with multiple
physiologic sensors including galvanic skin resistance, heat flux, body
temperature and near body ambient temperature. The armband is worn 7
consecutive days on the right upper arm over the triceps muscle and monitors
various physiological and movement parameters. The armband provides a
reproducible and accurate measure in subjects with chronic illness with
moderate functional limitations [57].

 8. Six questions are used to measure self-rated improvement after therapy
and the satisfaction of the patient. The questions: ‘How satisfied are
you with the effect of treatment’? ‘Is there a difference in how
you handle problems now compared to before treatment started?’ and
‘Is there a difference in your daily activities now compared to your
situation before treatment started?’ are scored on a 5-point Likert
scale (‘1’ is very content/much improvement and ‘5’
is very discontented/situation is worse). The question: ‘To what
extend did you achieve your personal treatment goals?’ is scored on a
10-point Likert scale, range 1–10. The questions: ‘Would you
recommend the treatment to other CFS patients?’ can be answered with
‘yes’, ‘no’ or ‘I don’t know’. The
question: ‘Do you still consider yourself a CFS patient?’ can be
answered with ‘yes’ or ‘no’ [58].

 9. Life satisfaction will be measured by the Life Satisfaction
Questionnaire, Dutch version (LSQ-DV). The LSQ-DV has one question on
general life satisfaction and eight questions about domain-specific life
satisfaction: self-care ability, leisure situation, vocational situation
(including housekeeping), financial situation, sexual life, partner
relationship, family life, contacts with friends and acquaintances.
Questions are answered on a 6-point Likert scale (‘1’ is very
dissatisfied, ‘6’ is very satisfied). The reliability of the
LSQ-DV has been proven to be moderate to good for most domains in a patient
group with chronic illness [59].

 10. Quality of life and utilities (health-related quality of life) will be
measured by means of the standard Dutch version of the EuroQol (EQ-5D)
[60]. The EQ-5D contains
five dimensions of health-related quality of life, namely mobility,
self-care, daily activities, pain/discomfort and depression/anxiety. Each
dimension can be rated at three levels: no problem, some problems and major
problems. The five dimensions can be summed into a health state. Utility
values are calculated for these health states, using preferences elicited
from a general population, the so-called Dolan algorithm [61]. The utility values derived from the
Dolan algorithm will be used to compute Quality Adjusted Life Years (QALYs).
The Dolan algorithm has been established using a general population from the
UK. Also a Dutch algorithm has become available that will be used in the
sensitivity analysis [62].

#### Treatment expectancy and credibility

Patients’ initial beliefs about the success of a given treatment have
been shown to have an important influence on the final treatment outcome. A
study by Smeets et al. (2008) [63]
found evidence of predictive validity of expectancy and credibility scored
by patients with chronic low back pain before following different active
interventions To measure treatment expectancy and credibility, 2 weeks after
the start of treatment, all participants will be asked to fill in the Dutch
version of the Devilly and Borkovec questionnaire [64].

#### Mediation

In order to understand how treatment works, mediation analyses are performed.
Two studies on mediation could not confirm the mediating role of physical
activity in reducing fatigue in CFS. Moss-Morris (2005) [21] investigated physical activity as a
mediator in the treatment effect of GET and Wiborg (2010) [65] in CBT. Since physical activity does
not mediate the outcome, other parameters have to be responsible for a
decrease of fatigue during therapy. In the model of Vercoulen et al.
[14], somatic attributions,
focussing on pain and fatigue, and low self-efficacy contribute to the
perpetuating of CFS complaints. Patients with CFS feel helpless and
surrendered to their complaints, making it difficult to change their
situation. During therapy patients learn to change cognitions into more
helpful cognitions, which increases self-efficacy. They learn to accept
their situation in the present, making choices based on helpful cognitions
and bodily symptoms other than pain and fatigue, and learn to focus on
getting better instead of focussing on complaints and somatic attributions.
Our hypothesis is that by increasing self-efficacy, decreasing somatic
attributions and increasing the present-centred attention-awareness during
activities first, behavioural changes can be made based upon these changes
and eventually the severity of fatigue will decrease.

There are no studies that we are aware of that determine the mediating role
of self-efficacy, somatic attributions and present-centred
attention-awareness. Mediation will be investigated by the three-step method
described by Baron and Kenny [66].
Before treatment (T1), 6 and 14 weeks after start of treatment (T2, T3),
CIS, SE28, CAL and MAAS are filled in by the patient in order to analyse
mediation at different moments during treatment phase.

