**Methods:**

One hundred twenty patients who meet the criteria of chronic fatigue
syndrome, fulfil the inclusion criteria and sign the informed consent form
will be recruited. Both treatments take 6 months to complete. The outcome
will be assessed at 6 and 12 months after the start of treatment. Two weeks
after the start of treatment, expectancy and credibility will be measured,
and patients will be asked to write down their personal goals and score
their current performance on these goals on a visual analogue scale. At 6
and 14 weeks after the start of treatment, the primary outcome and three
potential mediators—self-efficacy, causal attributions and
present-centred attention-awareness—will be measured. Primary outcomes
are fatigue severity and quality of life. Secondary outcomes are physical
activity, psychological symptoms, self-efficacy, causal attributions, impact
of disease on emotional and physical functioning, present-centred
attention-awareness, life satisfaction, patient personal goals, self-rated
improvement and economic costs. The primary analysis will be based on
intention to treat, and longitudinal analysis of covariance will be used to
compare treatments.

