### Aims of the study

The FatiGo trial is designed to address the following primary objectives:

 1. To assess the differences in treatment effect (change between baseline and
6-month follow-up in fatigue severity and quality of life) in patients with CFS
between individual multidisciplinary rehabilitation treatment (MRT) and
individual cognitive behavioural therapy (CBT).

 2. To assess the differences in long-term treatment effect (change between
baseline and 12-month follow-up in fatigue severity and quality of life) in
patients with CFS between the two treatments.

 3. To assess the difference in cost-effectiveness and cost-utility between MRT
and CBT from both a health care and societal perspective at 12-month
follow-up.

 4. To assess the differences in treatment effect in psychological symptoms,
self-efficacy, causal attributions, present-centred attention-awareness, impact
of disease on physical and emotional functioning, self-rated improvement and
life satisfaction between MRT and CBT (at 6- and 12-month follow-up).

The secondary objectives of this trial are:

 1. To assess the influence of patients treatment expectancy and credibility on
the effectiveness of treatment.

 2. To assess what baseline factors (other than the assigned treatment) predict a
change in fatigue and increase in quality of life in all participants.

 3. To evaluate whether changes in self-efficacy, changes in causal attributions
and/ or changes in present-centred attention-awareness (at baseline, 6 and 14
weeks after start of treatment) mediate changes in fatigue severity and changes
in quality of life after treatment.

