### Assessment and procedures

After inclusion, the research assistant contacts the patient to make an
appointment for the baseline assessment (T1). During T1 the patient is asked to
wear the activity monitor for one week and to fill in the following
questionnaires: 

 Checklist Individual Strength (CIS)

 Short Form 36 (SF-36)

 EuroQol- 5D (EQ-5D)

 Symptom Check List-90 (SCL-90)

 Self-Efficacy Scale-28 (SES 28)

 Causal Attribution List (CAL)

 Mindfulness Attention Awareness Scale (MAAS)

 Sickness Impact Profile-8 (SIP-8)

 Life Satisfaction Questionnaire, Dutch Version (LSQ-DV)

The patient is instructed on how to fill in the Tic-P, part II on health- and
non-health-related costs every month for 1 year. One week after baseline
assessment, the research assistant collects the activity monitor. The research
assistant gives the patient a blind envelope with the treatment conditions.
Treatments start within 4 weeks. Two weeks after the start of treatment, a
patient is asked to fill in the list of Borkovec and Devilly and the PSCG, part
1. At 3 and 9 months after T1 a patient is asked to fill in the Tic-P, part I at
home. Six months after the start of treatment the research assistant assesses
the patient again (T4). The patient is asked to wear the activity monitor and
fill in the same questionnaires as in T1 completed by the PSCG, part II
self-rated improvement questionnaire and Tic-P, part I. Twelve months after the
start of the treatment, the same assessment as in T4 will be repeated (T5). For
each patient the study takes 12 months.

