#### Mediation analyses

In the mediation analysis, we investigate whether self-efficacy, somatic
attributions and/or present-centred attention-awareness intervenes in the
relationship between treatment and outcome. Multiple regressions are used to
explore which factors mediate the outcome. Mediation is suggested when the
change in the putative mediating factors is significantly related to
treatment as the independent variable, outcome is significantly related to
treatment as the independent variable, and finally, the relationship between
outcome and treatment decreases (or goes to zero) when the change in the
mediation factor is entered into the equation [66].

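### The three-step mediation rule cannot show whether a mediator drives the fall in fatigue or follows it, although the hypothesis is about that order

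*Protocol article*

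**What the plan says.** The Mediation section of the protocol article states an order. The three mediators are to change during "activities first, behavioural changes can be made based upon these changes and eventually the severity of fatigue will decrease".

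The measurements are set out in the same section: "Before treatment (T1), 6 and 14 weeks after start of treatment (T2, T3"), and at those visits "CIS, SE28, CAL and MAAS are filled in by the patient in order to analyse mediation at different moments during treatment phase". The abstract gives the same timing: "At 6 and 14 weeks after the start of treatment, the primary outcome and three potential mediators" are measured. Under Assessment and procedures, patients at 6 months (T4) "fill in the same questionnaires as in T1 completed by the PSCG, part II", and this is repeated at 12 months (T5).

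The third secondary objective, under Aims of the study, puts the outcome later. It asks whether mediator changes at baseline, 6 and 14 "weeks after start of treatment) mediate changes in fatigue severity and changes in quality of life after treatment".

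The rule is under Mediation analyses. Mediation is suggested if (1) mediator change is significantly related to treatment, (2) outcome is significantly related to treatment, and (3) the relationship between "outcome and treatment decreases (or goes to zero) when the change in the mediation factor is entered into the equation".

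**The concern.** The hypothesis is about sequence, but nothing in the three conditions tests sequence. Conditions 1 and 2 ask only whether the arms differ on the mediator and on the outcome. Condition 3 asks only whether the treatment coefficient shrinks once mediator change is entered.

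Suppose fatigue has already fallen by week 14 in one arm. Those patients may report more control over their symptoms at week 14 because they feel better, and they will tend still to be less fatigued at 6 months. Early fatigue then feeds both the mediator and the later outcome. The treatment coefficient shrinks although the mediator does nothing. Taking the outcome later does not remove this, because the fatigue change present at the mediator visit is not in the model.

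At stake is the third secondary objective, and the information on mediators that the Discussion promises. A positive result would fit two opposite accounts: control over symptoms brings recovery, or recovery brings a sense of control. For fatigue, the CIS scores at T2 and T3 that bear on this are collected but not used in the stated rule.

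**Working it through.** The article gives no mediation figure to reproduce, so the check is of the stated rule itself.

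**Inputs from the article.** 48 analysed per arm, alpha 0.05, and a relevant difference of 0.5 SD (Sample size). The three conditions come from Mediation analyses.

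**Assumptions, not in the article.** Within-arm correlation r between mediator change and fatigue change at the mediator visit: 0.3 to 0.7. Correlation ρ between fatigue change at that visit and later fatigue change: 0.5 to 0.7. Early arm difference d in fatigue: 0, 0.5 or 1.0 SD.

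**A case in which the mediator has no effect.** With t = 0 or 1 for arm, e for independent standard normal noise (a fresh draw in each line), and negative fatigue change meaning improvement:

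- early fatigue change: F = −d·t + e
- mediator change, which only follows fatigue: M = −r·F + √(1−r²)·e
- later fatigue change: Y = ρ·F + √(1−ρ²)·e

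**Condition 3 by algebra.** The treatment coefficient for Y alone is −ρd. With M added it is −ρd(1−r²), so it shrinks by the fraction r²: 0.3² = 9%, 0.5² = 25%, 0.7² = 49%. For d = 0.5 and ρ = 0.7, the coefficient is −0.35 before, and after adding M:

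- r = 0.3: −0.35 × 0.91 = −0.319 (simulated −0.318)
- r = 0.5: −0.35 × 0.75 = −0.263 (simulated −0.263)
- r = 0.7: −0.35 × 0.51 = −0.179 (simulated −0.177)

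The coefficient therefore decreases, as condition 3 asks, with no mediation at all.

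**The full rule by simulation** (3000 trials per setting, 48 per arm): share of trials in which all three conditions are met.

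| r | ρ | d = 0 | d = 0.5 SD | d = 1.0 SD |
|---|---|---|---|---|
| 0.3 | 0.5 | 0.3% | 3.2% | 21.0% |
| 0.3 | 0.7 | 0.4% | 5.8% | 28.7% |
| 0.5 | 0.5 | 0.4% | 8.6% | 49.5% |
| 0.5 | 0.7 | 0.6% | 12.9% | 65.9% |
| 0.7 | 0.5 | 0.5% | 13.6% | 64.9% |
| 0.7 | 0.7 | 0.9% | 22.4% | 86.7% |

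Here the arm difference at the later visit is only what carries over (ρd). If it instead stays at full size to T4, with ρ = 0.7 and r = 0.3 to 0.5, the rule is met in about 8% to 18% of trials at 0.5 SD and 29% to 68% at 1.0 SD.

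**What limits these figures.** It is the power of conditions 1 and 2, not condition 3. Among trials that pass the first two (d = 0.5 SD at both visits, ρ = 0.7), condition 3 is met in 94%, 99.7% and 100% for r = 0.3, 0.5 and 0.7.

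**Adding early fatigue.** Across the settings in the table, the mediator coefficient is significant in 29% to 100% of trials without F in the model. With F added this falls to 3.8% to 5.9%, near the nominal 5%.

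**The opposite cases.** If the mediator truly acts after the visit at which it is measured, the adjusted model still detects it in 97% to 100% of trials. If a true mediator has already lowered fatigue by that visit, the adjusted model finds it in only about 5%. Adjustment is therefore informative about a lagged effect and blind to a fast one.

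**Quality of life.** The abstract says the primary outcome is measured at 6 and 14 weeks, and then names fatigue and quality of life as the primary outcomes. The Mediation section lists the CIS but no SF-36 at those visits. If that list is right, there is no interim quality-of-life score, and the adjustment cannot be made for that outcome.

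**The case against.** Four arguments go the other way.

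*The Aims already give a lag.* This is right: mediator change up to week 14 is set against change after treatment, so a reader who infers that only same-visit mediation is planned goes too far. But a later outcome does not settle direction, as the working shows.

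*Shared visits are not a fault.* A reader might infer that taking the CIS and the mediators together is the design error. It is not: the CIS at T2 and T3 is exactly what the adjusted analysis needs.

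*The plan's rule is stricter than a significant mediator coefficient.* A reader might infer that followers will usually pass as causes, since that coefficient is significant in 29% to 100% of the simulated trials. The article does not list its significance as a criterion. Its full rule needs the arms to differ on both mediator and outcome, so at the design difference it is met far less often. The supported word is "can", not "will".

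*This is a condensed article on a secondary objective.* Visit pairing and covariates may stand in a fuller analysis plan, and the article says only that mediation is suggested. That tempers the weight. The point does not rest on missing detail, however: the article states the rule and what enters it, and that rule does not address the stated order.

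On the abstract, the singular could be read as fatigue alone. But the heading under Primary outcome measures is also singular and covers both fatigue and quality of life, so the wording is ambiguous.

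**Conclusion.** The point holds in a limited form. The hypothesis is ordered and the rule is not, and a later outcome alone does not repair that. How often a non-causal mediator meets the full rule depends on the arm difference in early fatigue: about 3% to 22% of trials at 0.5 SD, 21% to 87% at 1.0 SD, under 1% with none. These ranges rest on the assumed correlations and on 48 analysed per arm. The modest figures at 0.5 SD give little comfort: once the arms differ on mediator and outcome, which is the only situation in which mediation would be claimed, condition 3 seldom rejects a follower.

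The documents do not support saying that such mediators will generally be taken for causes. For fatigue, the data already collected can test the ordered hypothesis in part. For quality of life, on the Mediation section's list of instruments, they cannot show direction. The point is worth acting on, but it concerns a secondary objective and does not touch the primary comparison.

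**What to change.** 1. In the Mediation and Mediation analyses sections, state the pairing: mediator change from T1 to T2 (or T3) with CIS-fatigue at a later visit (T3 or T4).
2. Report the stated model twice: as it stands, and adjusted for CIS-fatigue at T1 and at the mediator visit.
3. Add the reverse lag: early CIS change predicting later mediator change.
4. Claim support for the ordered hypothesis only if the adjusted lagged result agrees with the unadjusted one.
5. Reconcile the abstract with the Mediation section on what is measured at 6 and 14 weeks. If only the CIS was taken, say so, and state that quality-of-life mediation cannot show direction.

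The cost is wording and a few more regressions, with no new data. The downside is wider intervals for the mediator path, a weaker claim for quality of life, and an adjusted model that misses mediation which has already reached fatigue by the mediator visit. For that last reason the adjusted model should stand beside the stated one and not replace it.
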